## Abstract

**Background:**

The safety of laparoscopic total gastrectomy (LTG) for the treatment of gastric cancer remains lack of clinical evidence. The Chinese Laparoscopic Gastrointestinal Surgery Study (CLASS) Group recently launched a multicenter randomized clinical trial (CLASS02–01) to compare the safety of LTG for clinical stage I gastric cancer with the conventional open total gastrectomy (OTG).

**Methods:**

This CLASS02–01 trial is a prospective, multicenter, randomized, controlled, open, and non-inferiority trial. Two hundred patients who met the inclusion criteria and did not accord with the exclusion criteria will be randomly divided into LTG group (*n* = 100) and OTG group (n = 100). The primary purpose of this study is to evaluate the early operative morbidity and mortality of LTG compared with OTG for clinical stage I gastric adenocarcinoma. The second purpose is to evaluate the recovery course and compare the postoperative hospital stay of the patients enrolled in this study.

**Discussion:**

This CLASS02–01 trial is the first prospective randomized two-arm controlled study to determine the safety of LTG compared with OTG. Through this trial, we hope to show that experienced surgeons can safely perform LTG with lymphadenectomy for gastric cancer.

**Trial registration:**

ClinicalTrials.gov ID: NCT03007550. December 30, 2016.

## Background

Gastric cancer is still an important health problem nowadays, being the fourth most common cancer and the third leading cause of cancer-related death worldwide [1]. Age standardized mortality rates for gastric cancer are 14.3 per 100,000 in men and 6.9 per 100,000 in women [2]. Incidence shows clear regional and sex variations-rates are highest in Eastern Asia, Eastern Europe, and South America and lowest in Northern and Southern Africa [1]. More than 679,000 new cases and 498,000 deaths occur every year in China [2].

More than 20 years after the introduction of laparoscopic gastrectomy, many large-scale randomized controlled trials (RCT) have been conducted in Japan (JCOG0912 and JLSSG0901) [3, 4], Korea (KLASS01 and KLASS02) [5–9], and China (CLASS01) [10]. These trials are all designed to evaluate the non-inferiority of laparoscopic-assisted distal gastrectomy (LADG) to its open counterpart. No RCT for laparoscopic total gastrectomy (LTG) exists at this moment. At present, Japan (JCOG1401) [11] and Korea (KLASS03) [12] have planned or launched clinical studies on LTG. The standardization of techniques for esophagojejunal anastomosis in LTG has been difficult even for experienced surgeons [13]. China is one of the countries with the highest incidence of gastric cancer and surgeons have accumulated extensive experience through CLASS01 study. So, it’s time for conducting the clinical research on the safety of LTG for gastric cancer.

## Methods

### Objectives

This CLASS02–01 trial is a prospective, multicenter trial for laparoscopic total gastrectomy (LTG) and open total gastrectomy (OTG) in patients with clinical stage I (T1N0M0、T1N1M0、T2N0M0) gastric cancer. The primary purpose of this study is to evaluate the early operative morbidity and mortality and determine the safety of LTG compared with OTG for clinical stage I gastric adenocarcinoma. The second purpose is to evaluate the recovery course and compare the postoperative hospital stay of the patients enrolled in this study (Fig. 1).

**Fig. 1 Fig1:**
[figure not shown]
Study schema

### Study design

This CLASS02–01 trial is a prospective, multicenter, randomized, controlled, open, and non-inferiority trial comparing the safety of LTG (D1+/D2–10 lymphadenectomy) for clinical stage I (T1N0M0、T1N1M0、T2N0M0) gastric cancer in the upper and middle of their stomach with the conventional OTG.

### Ethic approval

Before enrollment of first patient, this study was approved from the institutional review boards of all research centers (14 tertiary hospitals) in China, including Zhongshan Hospital Fudan University (B2016-160R), Beijing Cancer Hospital, Southwest Hospital, Fudan University Shanghai Cancer Center, Fujian Medical University Union Hospital, The First Affiliated Hospital of Fujian Medical University, Guangdong General Hospital, The First Bethune Hospital of Jilin University, The First Affiliated Hospital Zhejiang University, Nangfang Hospital, The First Affiliated Hospital With Nanjing Medical University, Renji Hospital, West China Hospital, Sichuan University, and Chinese PLA General Hospital. Written informed consent will be obtained from all patients for the acquisition and use of anonymized clinical data before they are recruited, and all investigators will progress this study in accordance with the Declaration of Helsinki. This CLASS02–01 trial will be monitored by an independent data and safety monitoring committee (DSMC).

### Participating surgeons

To participate in this CLASS02–01 trial, the responsible surgeons should meet the following qualifications: first, completing at least 50 cases of OTG and LTG with D2 lymphadenectomy respectively; second, passing the blind review of surgery video. Briefly, the applicants should provide the videos of OTG and LTG in recent 3 months (three cases each) to the CLASS Research Council; CLASS Research Council will select two videos of OTG and LTG separately, and randomly appoint three experts to peer review blindly. When three experts unanimously approved it, the applicant will be permitted to participate in this study as a researcher.

### Sample size calculation

This is a non-inferiority verification study on clinical safety, with the early operative morbidity and mortality rate as the main index for safety evaluation. According to the previous reports, the morbidity and mortality rate for OTG is about 20%. Setting α=0.05, β = 0.2, and the noninferiority margin δ = 10%, the sample size required for each group is 90 cases. Considering that the maximum dropout rate for this clinical study is about 10%, the sample size is determined as 100 cases in each group.

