### Statistical analysis

Statistical analysis will be performed with SAS Software (version 9.3; SAS Institute, Cary, NC). The data are presented as the mean ± standard deviation for continuous variables and as a number for categorical variables. The statistical significance will be evaluated using χ^2^ test, Fisher’s exact test, t test, or rank sum test. The Newcombe’s method will be used to compare the 95% CIs (confidence intervals) for between-group differences of intraoperative and postoperative morbidity and mortality. All *P* values were two sided, and differences were considered significant at values of *P* < 0.05.

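### Ninety per group does not follow from the stated inputs: with 20% event rates in both arms and a 10-point margin, power is about 39–55%, not 80%

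*Protocol article*

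**What the plan says.** The Sample size calculation section of the protocol article frames the trial this way: "This is a non-inferiority verification study on clinical safety, with the early operative morbidity and mortality rate as the main index for safety evaluation". It takes one event rate from earlier reports, "the morbidity and mortality rate for OTG is about 20" per cent, and then states: "Setting α=0.05, β = 0.2, and the noninferiority margin δ = 10%, the sample size required for each group is 90 cases". A 10% dropout allowance raises 90 to 100 per group. No LTG rate is given, and the sidedness of α is not stated.

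The Statistical analysis section names the interval: "The Newcombe’s method will be used to compare the 95% CIs (confidence intervals) for between-group differences of intraoperative and postoperative morbidity and mortality". It adds: "All *P* values were two sided, and differences were considered significant at values of *P* < 0.05". For a non-inferiority conclusion read from the upper limit, a two-sided 95% interval corresponds to one-sided α = 0.025.

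**The concern.** In a non-inferiority design, the usual planning assumption is that the two true rates are equal. With 20% in each arm, a 10-point margin is small relative to the sampling error of 90 patients per group. The standard error of the difference is about 6 points, so the margin is only about 1.7 standard errors wide. Eighty per cent power needs about 2.5 (one-sided 0.05) or 2.8 (one-sided 0.025).

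If the figure is wrong, the trial lacks the power it claims for its primary endpoint. Should LTG be exactly as safe as OTG, the trial would more likely than not fail to show this under its own 95% interval. Such a failure could be misread as evidence of harm. It could also tempt the authors to fall back on a non-significant χ² or Fisher test, which is not evidence of non-inferiority.

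**Working it through.** **Inputs.** From the Sample size calculation section: OTG rate 0.20, margin 0.10, α = 0.05, β = 0.2, stated n = 90 per group, dropout 10%. From the Statistical analysis section: Newcombe 95% interval. Assumption, because none is stated: true LTG rate also 0.20. Since sidedness is not given, both one-sided 0.05 and one-sided 0.025 are shown.

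**1. Attempt to reproduce 90.** The usual formula is n = (z₁₋α + z₀.₈₀)² × [p_C(1−p_C) + p_T(1−p_T)] / (margin − (p_T − p_C))².

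- One-sided 0.05: (1.645 + 0.842)² × 0.32 / 0.01 = 6.183 × 32 = 197.8, so **198** per group.
- One-sided 0.025: (1.960 + 0.842)² × 0.32 / 0.01 = 7.849 × 32 = 251.2, so **252** per group.

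Other constructions do not give 90 either:

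| Construction | n per group |
|---|---|
| One-sided α = 0.10 | 145 |
| Continuity correction (one-sided 0.05 / 0.025) | about 218 / 271 |
| Variance taken at the margin, 20% v 30% (0.05 / 0.025) | 229–232 / 291–295 |
| Equivalence by two one-sided tests (0.05 / 0.025) | 275 / 337 |
| Superiority, 20% v 10% | 157–219 |
| Superiority, 20% v 30% | 231–313 |
| One-sample formula (0.05 / 0.025) | 99 / 126 |

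The dropout step is sound: 90 / 0.9 = 100. The fault is in the 90 itself.

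**2. Power of the planned design, 20% in both arms.** SE = √(0.32/n) and power = Φ(0.10/SE − z₁₋α).

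- n = 90: SE = 0.0596 and 0.10/SE = 1.677. Φ(1.677 − 1.960) = 38.9%; Φ(1.677 − 1.645) = 51.3%.
- n = 100: SE = 0.0566 and 0.10/SE = 1.768. Φ(1.768 − 1.960) = 42.4%; Φ(1.768 − 1.645) = 54.9%.

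As a check, every pair of binomial outcomes was enumerated, and non-inferiority was counted when the Newcombe upper limit was below 10 points:

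| Evaluable per group | 95% interval | 90% interval |
|---|---|---|
| 90 | 38.9% | 51.3% |
| 100 | 42.2% | 55.0% |

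**3. A tied result.** Suppose each arm has 20 events in 100. The Wilson 95% limits for 20/100 are 13.34% and 28.88%. The Newcombe upper limit for LTG minus OTG is 0 + √[(0.2888 − 0.20)² + (0.20 − 0.1334)²] = 0.111, or 11.1 points, which fails. With OTG at 20/100, LTG at 19/100 gives 10.02 points (fails) and 18/100 gives 8.9 points (passes). With a 90% interval the tie gives 9.3 points and passes, so the unsettled sidedness can decide the conclusion.

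**4. What would make 90 correct.**

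- A lower LTG rate. At 15.8% and one-sided 0.05: 6.183 × (0.16 + 0.158 × 0.842) / (0.10 + 0.042)² = 89.8. At 14.3% and one-sided 0.025: 7.849 × (0.16 + 0.143 × 0.857) / (0.10 + 0.057)² = 90.0.
- A wider margin with equal 20% rates: √(0.32 × 6.183/90) = 14.8 points, or √(0.32 × 7.849/90) = 16.7 points.
- Equal rates of about 7.9% (one-sided 0.05) or 6.1% (one-sided 0.025) with the 10-point margin.

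The article states none of these; the last two contradict its stated margin and OTG rate.

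**The case against.** The strongest reply is that the low power is conditional. It holds if LTG truly has a 20% event rate, and the article never says that equal rates were assumed. An article condenses a fuller protocol, which may contain a lower LTG rate. With LTG at 15.8% and a 90% interval, or 14.3% and a 95% interval, exact Newcombe power at 90 per group is 80.1% and 79.5%. This is why the power figures here always carry the 20%/20% condition. It does not rescue the sentence. The article prints inputs and a result said to follow from them, and the result depends on an unstated 4–6 point LTG advantage that appears nowhere in the text.

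A second reply is that the decision rule is inferred. The Statistical analysis section names the Newcombe 95% interval but does not say that its upper limit is set against 10 points, and its two-sided 5% level may refer only to the general tests. That is fair, and it makes sidedness a secondary point. The shortfall remains under the lenient reading: one-sided 0.05 with no dropout gives 55%.

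Third, the 39–55% range spans two sample sizes and two α levels. At the stated 90 it is 39–51%; at 100 it is 42–55%.

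Finally, restating the power discloses the weakness without repairing it, and the possible misreadings of a failed result are risks, not something the article announces. Both points are correct.

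**Conclusion.** The concern holds. The 90 per group is less than half of what the stated inputs require under equal true rates (90/198 = 45%; 90/252 = 36%). Under the article's own 95% interval, a trial of two equally safe operations has about a 58% (n = 100) to 61% (n = 90) chance of not showing non-inferiority.

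The result rests on a true LTG rate of 20%, the absolute 10-point margin as stated, 1:1 allocation, and non-inferiority judged on the upper confidence limit. The requirement of at least 198 does not depend on how the sidedness of α is resolved. It would fall to about 90 only with an assumed LTG rate of roughly 14–16%, which would have to be stated and defended. This must be corrected, because it is the basis for the size of the primary comparison.

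**What to change.** Rewrite the Sample size calculation paragraph so that it:

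- states that α is one-sided 0.025, to match the 95% interval in the Statistical analysis section, and says that the upper limit for LTG minus OTG is compared with 10 points;
- states the assumed LTG rate. If it was 20%, report power of about 42% for 100 per group and 39% for 90 evaluable. If a rate of about 14–16% was assumed, state and justify it, and show power at that rate and at 20%;
- keeps the 10-point margin, since widening it to fit the sample size would be a change made for convenience;
- says that an upper limit above 10 points is inconclusive, not evidence of harm, and that a non-significant difference test does not establish non-inferiority.

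The cost is wording in the protocol and analysis plan, and a less favourable power statement. No extra patients are needed to restate the figure. Actually reaching 80% power under equal rates would be a different decision: 198 to 252 evaluable per group, or 220 to 280 randomised with 10% dropout (198/0.9 = 220; 252/0.9 = 280).

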### Study population

The patient inclusion and exclusion criteria are as follows:

#### Inclusion criteria

Aged 18–75 years;Primary lesion is pathologically diagnosed as gastric adenocarcinoma, such as papillary adenocarcinoma, tubular adenocarcinoma, mucinous adenocarcinoma, poorly cohesive carcinoma (including signet ring cell carcinoma and other variants), and mixed adenocarcinoma;Clinical stage IA (T1N0M0) or IB (T1N1M0, T2N0M0) (According to AJCC-7th TNM staging system);Tumor located in the upper or middle third of the stomach, and curative resection is expected to be achievable by total gastrectomy with D1+/D2–10 lymphadenectomy (also apply to multiple primary cancers);No invasion to Z-line;BMI (Body Mass Index) < 30 kg/m^2^;No history of upper abdominal surgery (except for laparoscopic cholecystectomy);No prior treatment of chemotherapy, radiotherapy, targeted therapy, immunotherapy;No enlargement of splenic hilar lymph nodes;Preoperative performance status (ECOG, Eastern Cooperative Oncology Group) of 0 or 1;Preoperative ASA (American Society of Anesthesiologists) scoring: I-III;Sufficient organ functions;Written informed consent.

#### Exclusion criteria

Preoperative examinations indicate that the stage of the disease is clinical stage II/III/IV;Preoperative examination indicate enlargement of perigastric or retroperitoneal lymph nodes (min diameter ≥ 1.0 cm);Women during pregnancy or breast-feeding;Synchronous or metachronous (within 5 years) malignancies;Body temperature ≥ 38 °C before surgery or infectious disease with a systemic therapy indicated;Severe mental disease;Severe respiratory disease;Severe hepatic and renal dysfunction;Unstable angina pectoris or history of myocardial infarction within 6 months;History of cerebral infarction or cerebral hemorrhage within 6 months;Continuous systemic steroid therapy within 1 month (except for topical use);Gastric cancer complications (bleeding, perforation, obstruction) that requiring emergency surgery;Patients are participating or have participated in another clinical trial (within 6 months).

### Randomized grouping

In this study, the central dynamic, stratified randomization method is adopted, and the factors including age, gender, BMI, and investigators, are considered. After each case is enrolled, the research center will arrange the research assistant to send the information of included cases (age, gender, and BMI) to the data center. After analyzing the case information by the center randomization department, the case grouping will be determined.

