### Operation procedure

#### Laparoscopic total gastrectomy

The laparoscopic total gastrectomy is to be carried out with endotracheal intubation under general anesthesia. The peritoneal cytology examination should be first taken after entering the abdominal cavity. After the peritoneal cytology examination, the surgeon should explore the abdominal cavity to determine if there is any regional invasion or distant metastasis, including hepatic, peritoneal, mesenteric, or pelvic metastasis. Then, total gastrectomy with D1+/D2–10 lymphadenectomy will be performed according to the Japanese Gastric Cancer Treatment Guideline (Fourth edition, May. 2014) (Table 1). If clinical stage II or more diseases are diagnosed intraoperatively, D2 radical gastrectomy should be performed, and these patients will be excluded from this study. A proximal margin of at least 2 cm is recommended for T1 tumors, 3 cm is recommended for T2 or deeper tumors with an expansive growth pattern (Bormann I and II), and 5 cm is recommended for those with infiltrative growth pattern (Bormann III and IV). It is advisable to examine the proximal resection margin by Pathological Frozen Section routinely to confirm the negative proximal resection margin during the operation. The distal margin located in the duodenal bulb. The digestive tract reconstruction methods should be determined by the doctor in charge according to their experience and the specific intraoperative circumstances. Roux-en-Y reconstruction is recommended, and the linear and circle staplers are both acceptable. The laparoscopic operations inside abdominal cavity, including perigastric devascularization, lymph node dissection, and blood vessel ligation, must be performed using laparoscopic instruments. While, gastrectomy and digestive tract reconstruction could be completed with open approach through auxiliary incision (≤10 cm).

**Table 1 Tab1:** D1+/D2–10 lymphadenectomy

Lymph nodes	Non-Cardia GC		EGJA	
	cT1N0	cT1N1/cT2N0	cT1N0/cT1N1	cT2N0
No. 1	✔	✔	✔	✔
No. 2	✔	✔	✔	✔
No. 3	✔	✔	✔	✔
No. 4	✔	✔		
No. 5	✔	✔		
No. 6	✔	✔		
No. 7	✔	✔	✔	✔
No. 8a	✔	✔		✔
No. 9	✔	✔		✔
No. 10				
No. 11p	✔	✔		✔
No. 11d		✔		✔
No. 12a		✔		
No. 19				✔
No. 20				✔

*GC* Gastric cancer, *EGJA* Esophagogastric junctional adenocarcinoma

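### Allocation is balanced on age, gender, BMI and investigator, but the named analysis does not use them in its standard form, so the deciding interval is valid but may be somewhat too wide

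*Protocol article*

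**What the plan says.** The Study design section describes a "prospective, multicenter, randomized, controlled, open, and non-inferiority trial". The Ethic approval section lists "all research centers (14 tertiary hospitals) in China". Under Randomized grouping, "the central dynamic, stratified randomization method is adopted, and the factors including age, gender, BMI, and investigators, are considered".

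The Statistical analysis section then says: "The statistical significance will be evaluated using χ^2^ test, Fisher’s exact test, t test, or rank sum test". For the safety comparison it adds: "The Newcombe’s method will be used to compare the 95% CIs (confidence intervals) for between-group differences of intraoperative and postoperative morbidity and mortality". Testing is two-sided at the 5% level, so the upper limit of the 95% interval acts as a one-sided 0.025 test. The section mentions no stratum, covariate or model.

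The Sample size calculation section assumes a 20% event rate for open surgery, a margin of 10 percentage points, α = 0.05 and β = 0.2. It arrives at 90 evaluable patients per arm, or 100 after 10% dropout.

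**The concern.** Balancing the arms on prognostic factors reduces the true sampling variance of the difference in event rates. A standard error computed as if the arms were two simple independent samples does not register that reduction. The resulting interval then covers more often than its nominal level.

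In a superiority trial this is a mild inefficiency. In a non-inferiority trial the claim rests on one confidence limit, so excess width translates directly into a greater chance of failing to show non-inferiority when it is true. The design has paid for balance on four factors, and the named analysis does not collect the return.

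**Working it through.** **1. The plan's own figure.** The article gives no rate for laparoscopic surgery, so equal true rates of 20% are assumed. The usual formula is n per arm = (z₁₋α + z₀.₈)² × [0.2 × 0.8 + 0.2 × 0.8] / 0.10².

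- One-sided 0.05: (1.645 + 0.842)² × 0.32 / 0.01 gives 198.
- One-sided 0.025: (1.960 + 0.842)² × 0.32 / 0.01 gives 252.

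The stated 90 is not reproduced. The dropout step is: 90 / 0.9 = 100.

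**2. Power of the named interval.** Exact binomial enumeration of the Newcombe upper 95% limit falling below 10 points gives 38.9% at 90 per arm and 42.2% at 100 per arm.

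**3. What the factors could contribute.** Let R² be the share of outcome variance that the allocation factors explain. The article gives no value, so a range is shown. With variance multiplied by (1 − R²), 100 per arm and one-sided 0.025, power = Φ(0.10 / √[0.0032 × (1 − R²)] − 1.96).

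| Assumed R² | 0 | 2% | 5% | 10% | 15% | 20% |
|---|---|---|---|---|---|---|
| Power | 42.4% | 43.1% | 44.2% | 46.2% | 48.3% | 50.7% |

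**4. Simulation of an analysis that actually adjusts.** Set-up: 200 patients, dynamic allocation on three binary factors and 14 investigators (one per centre, an assumption), a true rate of 20% in both arms, and 1,500 runs per setting. The unadjusted analysis used a simple normal limit. The adjusted one used a linear model for the risk difference, with robust standard errors and all factors included. Assumed log-odds effects of the three factors and the between-investigator SD were: weak 0.3, 0.2, 0.3 and 0.3; moderate 0.6, 0.4, 0.6 and 0.5; strong 0.9, 0.5, 0.9 and 0.8.

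| Setting | R² | Mean unadjusted SE | Actual SD of the difference | Ratio | Power, unadjusted | Power, adjusted |
|---|---|---|---|---|---|---|
| Weak | 2.1% | 0.0561 | 0.0570 | 0.98 | 43.6% | 43.5% |
| Moderate | 6.6% | 0.0563 | 0.0551 | 1.02 | 44.9% | 46.4% |
| Strong | 13.8% | 0.0562 | 0.0526 | 1.07 | 42.9% | 47.2% |

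Monte Carlo error is about √(0.44 × 0.56 / 1500) = 1.3 points on each power and about 1/√3000 = 1.8% on each SD, so the 0.98 is compatible with 1. A separate simulation of the same kind moved power from 45% to 44% with no prognostic effect, by under 1 point with modest effects, and from 43–44% to 46–49% with strong ones.

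**5. Where the gain comes from.** In the strong setting, adjusting for the three patient factors alone gives 44.5%; adding investigators gives 47.2%. The actual SD barely changes with full adjustment (0.0526 to 0.0520). Balance has already removed most of the variance, and adjustment mainly lets the standard error show it.

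**6. The same effect on the interval.** With 20% observed in both arms of 100, the half-width is 1.96 × √(0.32/100) = 11.1 points. Scaled by 0.0526 / 0.0562 it is 10.4 points, still above the margin.

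**The case against.** **The mismatch is partly read from silence.** The section never says that the analysis is unadjusted or unstratified. Its list of tests is generic, a stratified Newcombe interval exists, and the analysis plan is not shown. A reader might infer that the plan rules out adjustment; the article does not support that. What stands is narrower: the article names the method for the deciding interval, and in standard form that method ignores the allocation factors.

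**No validity problem.** This is right. The error runs in the conservative direction, so false claims of non-inferiority do not become more likely.

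**A larger gain might be claimed.** With a between-investigator SD of 0.8 to 1.3 on the log-odds scale, substituting the true standard error lifts power from about 44% to 47–50%. Those figures analyse no adjusted estimator. The SDs also imply risks of roughly 9% against 32% (SD 0.8) or 4% against 38% (SD 1.3) for investigators one SD below and above average. Nothing in the article supports such spread. The entry requirements under Participating surgeons (at least 50 cases of each operation and unanimous blind video approval) and the photographic review under Quality control point the other way.

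**Adjustment can cost something.** Also right. In the weak setting the adjusted SD was 0.0577 against 0.0570. A logistic model with arm, age, gender, BMI, stage and 14 centres has about 18 terms for 0.2 × 200 = 40 expected events. With 200/14 ≈ 14.3 patients per centre, the chance of at least one centre without events is about 1 − (1 − 0.8^14.3)^14 ≈ 44%, even without centre differences. Ordinary maximum likelihood cannot estimate such a centre's effect.

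**Clinical stage.** A reader might infer that omitting it is an error, because Table 1 varies the "D1+/D2–10 lymphadenectomy" stations by clinical stage. The article does not show that stage predicts 30-day morbidity. Using it is a preference.

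**Conclusion.** The point holds as a matter of modest efficiency and of consistency between design and analysis. The named analysis does not, in its standard form, use the four factors on which allocation is balanced. The deciding interval is therefore valid to conservative, with a standard error about 0 to 7% too large and a power cost of about 0 to 5 percentage points. The lower end applies if the factors are weakly prognostic, and the upper end only if they are strong.

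These figures rest on equal true rates of 20%, 100 patients per arm, 14 investigators and assumed prognostic strengths. The mismatch itself is clear; the size of the benefit is uncertain.

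It would be wrong to conclude that adjustment rescues the trial's power. Reaching 80% with 90 per arm would need the factors to explain about 55% of outcome variance at one-sided 0.05, or 64% at one-sided 0.025. The shortfall comes from the Sample size calculation section.

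**What to change.** Before the data are analysed, prespecify a primary risk difference that accounts for the allocation factors, by one of two routes:

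- a Mantel-Haenszel stratified Newcombe or Miettinen-Nurminen interval over centre or investigator, with small ones pooled by a rule fixed in advance; or
- a standardised risk difference adjusted for age, gender and BMI, with investigators pooled or handled by a method that tolerates sparse strata.

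Compare the upper limit of its 95% interval with 10 percentage points. Keep the unadjusted Newcombe interval as a sensitivity analysis. Adding clinical stage as a covariate is optional.

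If the unseen analysis plan already does this, one sentence saying so is enough. The cost is wording and a little programming: age, gender and BMI already go to the data centre at enrolment, and investigator is an allocation factor. The statistical downside is a negligible loss of precision (about 1 point of power at most in the simulations) if the factors turn out not to be prognostic. Correct the sample size and power statement separately.
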